#### 1.1.12 Clinical Experience with BSAM-2/Alhydrogel+CPG 7909 to date

The Phase 1 study of BSAM-2/Alhydrogel®+CPG 7909 described in this protocol began vaccinations at the Center for Immunization Research, Washington, DC, in June, 2009. As of September 30, 2009, a total of 30 malaria naïve US volunteers have been enrolled to receive up to 3 doses of either 40 or 160 µg BSAM-2 with 560 µg CPG 7909. Local adverse events have been as expected, with mild or moderate injection site pain. Systemic adverse events after first or second vaccination have reached Grade 3 severity in 4 volunteers (Grade 3 malaise in 2 volunteers, and Grade 3 fever and headache in 2 additional volunteers). Two volunteers have been withdrawn from vaccinations due to these adverse events. The events typically occur within 24 hours of vaccination and resolve within several hours of administration of acetaminophen or ibuprofen. Transient mild or moderate neutropenia has also been seen, as in previous studies with CPG 7909.

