## 3. STUDY DESIGN

### OVERALL DESIGN

This is a dose escalating multi-site Phase 1 clinical trial of the blood stage malaria vaccine candidate BSAM-2/Alhydrogel®+CPG 7909. Dose escalation will occur in the first part of the study, conducted in malaria-naïve adults at the Johns Hopkins Center for Immunization Research (CIR), in Washington, DC. Fifteen (15) participants will receive 40 µg BSAM-2/Alhydrogel® + 500 µg CPG 7909 (saline), with a group of 5 vaccinated first, followed approximately 2 weeks later by a group of 10. Providing halting rules are not met, an additional 15 participants will receive 160 µg BSAM-2/Alhydrogel® + 500 µg CPG 7909 (saline), also on a similar staggered schedule. All participants will receive 3 doses of vaccine administered IM, with the first 2 doses approximately 2 months apart and the third dose 6 months after the first. After the Safety Monitoring Committee reviews the safety data (through Study Day 63) of the last group to be vaccinated in the US, the second part of the study will be conducted in semi-immune adults in Bancoumana, Mali. This part of the study will be single-blinded and will include a comparator group. The comparator group in Mali will allow for better interpretation of antibody response in a population which has pre-existing immunity, particularly antibodies to the vaccine antigens, and which may experience malaria infection during the vaccination period, which would also affect antibody levels. Use of a comparator vaccine and blinding will also allow for more objective assessment of adverse events in this population, which has a higher rate of febrile illness and other clinical events that could be perceived as related to vaccination. Thirty (30) participants in Mali will be randomized 1:1 to receive the highest safe dose of BSAM-2/Alhydrogel®+CPG 7909, as determined at the SMC review, or the comparator vaccine (Euvax B/ Hepatitis B Vaccine, Recombinant), on a staggered schedule as in the US. The study vaccination schedule is outlined in **Table 2** below.

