## STUDY ENDPOINTS

### 3.1.1 Primary Endpoints

The incidence and severity of systemic and local adverse events

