**Study Day 720 ± 14 Days (Mali)**

An additional visit to the study clinic will be made and the volunteer will be asked about the development of any autoimmune disease or other serious illness and given contact information should an autoimmune disease develop, as above. Adverse events occurring during the extended passive follow up period will be captured as per usual in Mali.

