#### 11.1.1 Primary Objective

The primary objective of this study is to assess safety and reactogenicity of BSAM-2/Alhydrogel®+CPG 7909 in malaria-naïve US adults and semi-immune Malian adults.

- a. The frequency of systemic and local AEs will be summarized.
- b. A line listing of each clinical and laboratory AE classified as local, solicited, or other will be displayed in tables stratified by vaccine allocation and study site.
- c. AEs will be summarized by severity and relationship to vaccine.
- d. The proportion of subjects with at least 1 adverse event will be compared by vaccine and/or dose group within each study site, and tests performed to assess whether these groups differ with respect to these proportions. To see if there is a difference in adverse events between the initial vaccination and the subsequent vaccinations, a sign test will be performed, where the response for each subject is the difference between the numbers of adverse events in the 2 weeks following each vaccination.
- e. SAEs occurring within the study period will be listed by relationship to vaccine.

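### The only between-group safety test uses any adverse event, with no window, grade, type or relatedness limit, so it is likely to sit near ceiling and then say little about reactogenicity

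*Protocol*

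**What the plan says.** The primary endpoint in section 3.1.1 is "The incidence and severity of systemic and local adverse events", so severity is part of it.

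Section 11.1.1 lists five items, (a) to (e). Items (a), (b), (c) and (e) are summaries or listings; item (c), for example, reads "AEs will be summarized by severity and relationship to vaccine". Testing appears only in item (d), which has two parts:

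- Between groups: "The proportion of subjects with at least 1 adverse event will be compared by vaccine and/or dose group within each study site", with "tests performed to assess whether these groups differ with respect to these proportions". No test is named, and no window, grade, event type or causality category is given.
- Within subject: a sign test of first against later vaccinations, based on "the difference between the numbers of adverse events in the 2 weeks following each vaccination". This part does have a window.

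The adverse event definition in section 9 takes in events whether or not related to vaccination, intercurrent illnesses and laboratory-detected changes. Appendix C starts local reactions at easily tolerated pain or any erythema above 0 mm. Active follow-up is about 52 weeks from the first injection. For Mali, the Study Day 720 entry adds: "Adverse events occurring during the extended passive follow up period will be captured as per usual in Mali".

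**The concern.** A subject with one day of mild arm soreness, or an unrelated illness months after the last dose, scores the same as a subject with severe systemic reactions after each injection.

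Almost anyone given three injections and followed for a year may have at least one such event:

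- In the US part, both dose groups receive the same CPG 7909 dose. The interim account in section 1.1.12 says: "Local adverse events have been as expected, with mild or moderate injection site pain".
- In Mali, the comparator is also an injected, aluminum-adsorbed vaccine. The Overall Design section describes the population as one "which has a higher rate of febrile illness and other clinical events that could be perceived as related to vaccination". That is the stated reason for the comparator and the blinding, yet the tested proportion merges this background with reactogenicity. Section 9.1.3 classes clinical malaria as unrelated to vaccination, but as an intercurrent illness it would still count here.

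The reactions that matter most so far are of another kind. Section 1.1.12 reports Grade 3 malaise, fever or headache in 4 of 30 US volunteers, typically within 24 hours of vaccination. An unrestricted any-event proportion does not separate these from trivial events.

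**Working it through.** **Inputs from the protocol.** 15 per group, with 12 as the number the sample size is built on; Mali randomized 1:1 (15 v 15).

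**Assumptions.** Fisher's exact test, two-sided 5% (the protocol names no test and no alpha). All event rates below are assumed, because the protocol gives no any-event proportion for any group.

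**The plan's own figure.** The chance of seeing at least one event in 12 subjects at 0.125 each is 1 − 0.875^12 = 0.799, which reproduces the stated 0.80. It is a within-group detection probability and says nothing about a between-group test.

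**What the test needs.** If one group has 15/15 with an event:

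- 11/15 in the other gives p = 0.10;
- 10/15 (67%) gives p = 0.042.

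So when one group is certain to be at 100%, power is the probability that a binomial(15, q) count is 10 or fewer, where q is the other group's rate.

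| Any-event rates | Power, 15 v 15 |
|---|---|
| 100% v 95% | 0.0006 |
| 100% v 90% | 0.013 |
| 95% v 90% | 0.006 |
| 100% v 80% | 0.16 |
| 100% v 70% | 0.48 |
| 100% v 60% | 0.78 |
| 100% v 50% | 0.94 |

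**How quickly background events fill the endpoint.** With background events at a constant rate λ per person-year, P(at least one in a year) = 1 − exp(−λ). An assumed λ of 2 gives 1 − exp(−2) = 0.86; an assumed λ of 3 gives 0.95.

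**How background dilutes a real difference.** Let r be the probability of a vaccine reaction and b that of a background event, taken as independent. Then p = 1 − (1 − b)(1 − r). Take an assumed r of 90% v 30%. At b = 0.5, for example, p is 1 − 0.5 × 0.1 = 0.95 against 1 − 0.5 × 0.7 = 0.65.

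| Background b | Any-event rates | Power, 15 v 15 |
|---|---|---|
| 0 | 90% v 30% | 0.89 |
| 0.3 | 93% v 51% | 0.63 |
| 0.5 | 95% v 65% | 0.40 |
| 0.7 | 97% v 79% | 0.13 |
| 0.9 | 99% v 93% | 0.002 |

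The vaccine effect is the same in every row; only the unrelated background changes.

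**What a narrower endpoint can do.** For a windowed, graded endpoint, power depends on the contrast assumed: 0.74 at 60% v 10%, 0.52 at 40% v 5%, 0.33 at 40% v 10% and 0.11 at 40% v 20%. A Grade 3-only test needs 5/15 v 0/15 (p = 0.042; 4/15 v 0/15 gives 0.10). At the pooled US rate of 4/30 = 13% against 0%, its power is about 4%.

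**The case against.** The strongest reply is that this test is not how the primary objective is answered. The Description of Statistical Methods calls the study exploratory and aimed at estimating event rates with 95% confidence intervals. Events are summarized by severity and relationship, and listed by vaccine allocation and site. The halting rules act when two or more subjects in a cohort have a related Grade 3 systemic event, and the Safety Monitoring Committee reviews cumulative data before Mali starts. No decision in the protocol depends on the p-value from item (d). All of this stands. A reader might infer that the trial as a whole would miss severe reactions; the documents do not support that.

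A second reply is that the ceiling is assumed. This also stands. A reader might infer that the proportion will be near 100% in every group and that the test cannot show a difference. No any-event rate is given, least of all for the hepatitis B arm, and a comparator at 50% to 60% would leave useful power against 100%. Nor does every laboratory deviation count: Appendix D sets grading thresholds.

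A third reply is that windows and event categories are often left to an analysis plan, which is not shown here. This carries less weight. The protocol does state the endpoint to be compared, and it gives a window to the sign test in the same item but none to the group comparison.

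**Conclusion.** The point holds as a defect of one test. The single between-group comparison for the primary endpoint ignores severity, which is half of that endpoint, and pools vaccine reactions with a year or more of unrelated events. If any-event rates are about 90% or more in both groups, which the definition, the Grade 1 thresholds and the length of follow-up make likely, power is about 1% or less. At 100% v 80% it is 16%; at 100% v 60% to 50% it is 78% to 94%. These figures assume a two-sided 5% Fisher exact test with 15 per group and rates that the protocol does not state.

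A non-significant result near ceiling should not be read as evidence of similar reactogenicity. The documents do not say that anyone would read it that way, and the descriptive tables would sit beside it. The change is worth making because a better comparison is available from data already collected and graded.

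**What to change.** In section 11.1.1(d), replace the between-group comparison with the following, labelled exploratory:

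1. The proportion with any solicited local event of Grade 2 or higher within the 2 weeks after any dose, which is the window already used for the sign test.
2. The same for solicited systemic events.
3. The maximum grade per subject, by an exact rank-sum or trend test.

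Give each difference in proportions with an exact 95% confidence interval, and name the test and its level. Report Grade 3 events and any adverse event descriptively with confidence intervals; a Grade 3 test at this size has too little power to be useful.

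The cost is a change of wording and a few table rows. Visits on Days 3, 7 and 14 after each dose, and the Appendix C grading, already supply the data. The downside is a few more exploratory comparisons. Power for the new comparisons is not assured either, so the intervals should carry the interpretation.

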**Study Day 14  $\pm$ 2 Days**

1. Perform basic history and focused physical examination (including injection site), emphasizing examination of any acute complaints.
2. Record vital signs.
3. Obtain urine for dipstick testing. Obtain urine or serum for  $\beta$ -hCG testing.
4. Obtain approximately 15 mL of blood for CBC with differential and platelet count, ALT, creatinine, anti-AMA1 and anti-MSP142 ELISA.

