**Study Day 70 $\pm$ 2 Days (14 Days after Second Vaccination)**

1. Perform basic history and focused physical examination (including injection site), emphasizing examination of any acute complaints.
2. Record vital signs.
3. Obtain urine for dipstick testing. Obtain urine or serum for  $\beta$ -hCG testing.
4. Obtain approximately 40 mL of blood for CBC with differential and platelet count, ALT, creatinine, anti-dsDNA, anti-AMA1 and anti-MSP142 antibody ELISA, T cell studies, and GIA.
5. Obtain blood for malaria smear and filter paper collection (Mali only).

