**Study Day 134  $\pm$ 2 Days (14 Days after Third Vaccination) (Mali)**

1. Perform basic history and focused physical examination (including injection site), emphasizing examination of any acute complaints.
2. Record vital signs.
3. Obtain urine for dipstick testing. Obtain urine or serum for  $\beta$ -hCG testing.
4. Obtain approximately 40 mL of blood for CBC with differential and platelet count, ALT, creatinine, anti-dsDNA, anti-AMA1 and anti-MSP142 antibody ELISA, B and T cells, and GIA.
5. Obtain blood for malaria smear and filter paper collection

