### DEFINITIONS

#### ADVERSE EVENTS (AE)

An adverse event (AE) includes any unfavorable or unintended change in anatomical, physiological, or metabolic functions as indicated by physical signs, symptoms, and/or laboratory-detected changes occurring in any phase of the clinical study, whether associated with the study vaccine or active comparator, and whether or not considered vaccination related. This includes an exacerbation of pre-existing conditions and intercurrent illnesses. All AEs must be graded for severity and assessed for relationship to the investigational vaccine as described below.

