#### 9.1.2 Determination of Severity

Severity of AEs will be assessed by the investigator as described in **Appendixes C, D, and E**. AEs not included in the Appendixes will be graded for severity using the followings definitions:

|                             |                                                                                                                                                                  |
|-----------------------------|------------------------------------------------------------------------------------------------------------------------------------------------------------------|
| Grade 1 (Mild):             | No effect on activities of daily living                                                                                                                          |
| Grade 2 (Moderate):         | Partial limitation in activities of daily living (can complete $\geq 50\%$ of baseline), or treatment given; no or minimal medical intervention/therapy required |
| Grade 3 (Severe):           | Activities of daily living limited to $< 50\%$ of baseline, medical evaluation/therapy required                                                                  |
| Grade 4 (Life-threatening): | Extreme limitation in activity, significant assistance required; immediate medical intervention or therapy required to prevent death                             |
| Grade 5:                    | Death                                                                                                                                                            |

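### The sign test of first-dose against later-dose adverse events counts laboratory findings, but two tests (anti-dsDNA; malaria smear in Mali) are scheduled within 2 weeks of doses 2 and 3 and not of dose 1

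*Protocol*

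**What the plan says.** Item d of section 11.1.1 asks whether AEs differ between the first and the subsequent vaccinations. It uses a sign test in which "the response for each subject is the difference between the numbers of adverse events in the 2 weeks following each vaccination". The count is not restricted by type of event, relatedness or means of detection.

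Laboratory findings belong to this analysis. Item b of the same section calls for "A line listing of each clinical and laboratory AE classified as local, solicited, or other". The AE definition in section 9 covers "physical signs, symptoms, and/or laboratory-detected changes occurring in any phase of the clinical study", whether or not related to vaccine. Section 9.1.2 adds that "AEs not included in the Appendixes will be graded for severity using the followings definitions", so an event does not need a row in a toxicity table to be an AE.

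The visit schedule in section 6.5 fixes the tests after each dose. For Day 14 it reads "Obtain approximately 15 mL of blood for CBC with differential and platelet count, ALT, creatinine, anti-AMA1" and continues with the remaining ELISA; neither anti-dsDNA nor a smear is listed. Day 70, 14 days after dose 2, adds anti-dsDNA at both sites and, for Mali, the instruction "Obtain blood for malaria smear and filter paper collection". After dose 3, Day 194 (US) adds anti-dsDNA and Day 134 (Mali) adds both tests. Appendix B agrees.

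**The concern.** A within-subject comparison of event counts is fair only if events are looked for equally in the windows compared. Here the later windows contain one extra scheduled test in the US and two in Mali. A raised anti-dsDNA or a symptom-free positive smear that was recorded as an AE could add to the count after dose 2 or 3. It could not add to the count after dose 1, when nobody looked. The direction is therefore known.

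The test serves the primary objective, and its one question is whether AEs change after the first dose. The discussion of immunization risks says that anti-dsDNA has generally appeared after multiple vaccinations, but no sample shortly after dose 1 exists to compare with. The Mali comparator arm does not remove the problem, because each subject is compared with himself or herself.

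**Working it through.** **1. Scheduled tests in the 2 weeks after each dose** (section 6.5, checked against Appendix B; 14-day visits are Day 14, Day 70, and Day 194 in the US or Day 134 in Mali).

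| Assessment | Dose 1 | Dose 2 | Dose 3 |
|---|---|---|---|
| Clinical evaluation, CBC, ALT, creatinine, dipstick | same pattern | same pattern | same pattern |
| Anti-dsDNA, both sites | 0 | 1 | 1 |
| Malaria smear, Mali | 0 | 1 | 1 |

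The first row was checked within each site. For example, the Day 7 creatinine is taken only in Mali, and the same holds 7 days after doses 2 and 3. Anti-dsDNA and a smear are also done at screening. In Mali, smears are listed before the injection on Days 0, 56 and 120. These lie before dosing and are alike for every dose, so they do not alter the 0/1/1 pattern.

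**2. The plan's own figure.** None is given for the sign test. The only design figure, in the sample size section, is 1 − 0.875^12 = 0.799. It reproduces the stated 0.80 and has no bearing here.

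**3. Illustration.** The protocol gives no alpha, no AE rate per dose and no yield for the extra tests. I assume:
- an exact two-sided sign test at 0.05;
- equal true Poisson AE counts with mean m after dose 1 and after a later dose;
- one extra AE in the later window with probability q.

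Let T be the probability that the two true counts tie, and S the probability that the later count is lower by exactly one. Then

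P(more later) = (1 − T)/2 + qT; P(fewer later) = (1 − T)/2 − qS.

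- m = 0.5: T = 0.4658, S = 0.2079. At q = 0.30: 0.2671 + 0.1397 = 0.4068 against 0.2671 − 0.0624 = 0.2047. The share of untied subjects with more later is 0.4068/0.6115 = 0.665.
- m = 1: T = 0.3085, S = 0.2153. At q = 0.30: 0.4383 against 0.2812, a share of 0.609.
- At q = 0.10 the shares are 0.560 (m = 0.5) and 0.537 (m = 1).

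Enumerating all combinations of more, fewer and tied for 15 subjects gives the two-sided rejection probability when dose has no true effect:

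| Mean AEs per window | q = 0 | q = 0.10 | q = 0.30 |
|---|---|---|---|
| 0.5 | 2.0% | 2.8% | 9.4% |
| 1 | 2.3% | 2.7% | 6.0% |
| 4 | 2.4% | 2.5% | 3.2% |

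The q = 0 column is below 5% because the exact test is discrete. It is also the result under the fix.

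**4. A low-yield case.** The protocol's background on CPG 7909 reports raised anti-dsDNA in 1 volunteer of a 56-subject trial (1/56 = 1.8%) and in 4 subjects of a 58-subject trial in HIV-infected adults (4/58 = 6.9%). Denominators for those who received CPG 7909 are not given, so the true rates may be higher. With q = 0.02-0.07 and means of 0.5-4, rejection at n = 15 is 2.0-2.5%, hardly different from no asymmetry.

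**The case against.** The strongest objection is that one link is inferred. The protocol nowhere says that a raised anti-dsDNA or a symptom-free positive smear is recorded as an AE, and Appendix D has no row for either. Its own malaria event is the clinical episode, classed as unrelated to vaccine. Symptomatic illness is sought after every dose, with smears at unscheduled visits too. This stands as a limit: the bias arises only to the extent that such results are recorded as AEs. It does not remove the point. The AE definition is wide enough to take them in, ungraded types are provided for, and item d is not confined to related events.

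The second objection is size. The 10-30% yield has no source in the protocol, and a mean of 0.5-1 AE per window is the unfavourable end of the range. Both criticisms stand.

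Three stronger readings are tempting and are not supported:

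- **That the tests occur only after doses 2 and 3.** This is true of the 2-week windows, not of the whole schedule.
- **That false rejection reaches about 22%.** This needs 30 subjects, a mean of 0.5 and q = 0.30. In Mali, where a high yield is conceivable, 30 subjects means pooling vaccine and hepatitis B recipients; each arm has 15.
- **That the plus or minus 2 day allowance on the 14-day visit adds to the bias.** It applies equally after every dose, so it adds noise without direction. It also weakens the bias. If visits were spread evenly over Days 12-16, 2 of 5 would fall after 2 weeks, q = 0.30 would become 0.18, and the 9.4% above would fall to 4.5%.

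Finally, the study is described as exploratory, no halting rule uses this test, and line listings would show which events drove a result. That limits the consequence. It is still more than detail left to an analysis plan, because the protocol itself fixes the response variable in a way that does not match its own schedule.

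**Conclusion.** The point holds in a limited form. The schedules differ as described, the sign test counts every AE in the window, and any resulting bias runs towards more AEs after later doses. Whether it operates depends on how positive anti-dsDNA results and symptom-free smears are recorded, which the protocol does not state.

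Its size cannot be determined from the protocol. It is probably small in the US, where only anti-dsDNA is added. It could matter in Mali if positive smears are common. Under the assumed yields of 10-30% and 0.5-1 AE per window, two-sided rejection at 15 per arm rises from about 2% to about 3-9%; at 4 AEs per window it stays near 3% or below. A reader might infer that later doses are bound to look worse. The protocol supports only a possible bias of known direction and unknown size. Correcting it is worthwhile because the test addresses the primary objective and the correction is nearly free.

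**What to change.** In section 11.1.1, item d, state that the sign test counts only AEs found by assessments scheduled identically after every dose at that site: clinical evaluation, local and solicited symptoms, CBC, ALT, creatinine and urine dipstick. State that AEs first detected by the scheduled anti-dsDNA test or the scheduled malaria smear are listed separately, by dose and site.

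Keep the fixed 2-week window. Ending it at the 14-day visit would give windows of 12 to 16 days that could differ within a subject.

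The cost is one or two sentences, with no new data or visits. No safety information is lost, because items a to c still report every event.
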